# An open label randomized multicentre phase IIIb trial comparing parenteral substitution versus best supportive nutritional care in subjects with pancreatic adenocarcinoma receiving 5-FU plus oxaliplatin as 2^nd ^or higher line chemotherapy regarding clinical benefit - PANUSCO

**DOI:** 10.1186/1471-2407-9-412

**Published:** 2009-11-27

## Abstract

**Background:**

Pancreatic cancer is an extremely aggressive malignancy. Subjects are afflicted with a variety of disconcerting symptoms, including profound cachexia. Recent data indicate that the outcome of oncological patients suffering from cancer cachexia could be improved by parenteral nutrition and that parenteral nutrition results in an improvement of quality of life and in prolonged survival.

Currently, there is no recommendation of routine use of parenteral nutrition. Furthermore, there is no clear recommendation for 2^nd ^line therapy (or higher) for pancreatic adenocarcinoma but often asked for.

**Methods/Design:**

PANUSCO is an open label, controlled, prospective, randomized, multicentre phase IIIb trial with two parallel arms. All patients will be treated with 5-fluorouracil, folinic acid and oxaliplatin on an outpatient basis at the study sites. Additionally, all patients will receive best supportive nutritional care (BSNC). In the experimental group BSNC will be expanded with parenteral nutrition (PN). In contrast, patients in the control group obtain solely BSNC. Parenteral nutrition will be applied overnight and at home by experienced medical staff.

A total of 120 patients are planned to be enrolled. Primary endpoint is the comparison of the treatment groups with respect to event-free survival (EFS), defined as the time from randomization till time to development of an event defined as either an impairment (change from baseline of at least ten points in EORTC QLQ-C30, functional domain total score) or withdrawal due to fulfilling the special defined stopping criteria for chemotherapy as well as for nutritional intervention (NI) or death from any cause (whichever occurs first).

**Discussion:**

The aim of this clinical trial is to evaluate whether parenteral nutrition in combination with defined 2^nd ^line or higher chemotherapy has an impact on quality of life for patients suffering from pancreatic adenocarcinoma.

**Trial registration:**

Current Controlled Trials ISRCTN60516908.

## Background

Pancreatic cancer is an extremely aggressive malignancy characterized by extensive invasion, early metastasis, and marked cachexia. The yearly incidence of pancreatic cancer overlaps the mortality rate and the 5-year survival rate is less than 5% [1]. Subjects are afflicted with a variety of disconcerting symptoms, including profound cachexia and deterioration in performance status (PS), even when their tumour burden is low [2,3]. Therefore, one of the most important therapeutic targets is the improvement of quality of life (QoL) [4].

Cachexia is a strong independent predictor of mortality, poor therapeutic response, diminished functional capacity, and reduced QoL. It is defined as the debilitating state of involuntary weight loss, often connected with anorexia, tissue wasting, malnutrition, and inability for natural nutrition intake. The combination of these symptoms is also named "cancer anorexia-cachexia syndrome" [4]. The most important phenotypic feature is muscle wasting and functional impairment as a result of increased protein degradation and reduced protein synthesis or both [5]. In addition, it is a life-threatening and debilitating syndrome for 50% of all cancer subjects [5]. Compared to other solid tumours, the pancreatic cancer has the highest incidence for cancer cachexia (CC), as much as 80% at the time of diagnosis [4].

It has to be considered that the full effect of CC can not be identified by weight loss alone. Reduced food intake and systemic inflammation are also involved. Therefore, a multifactor cachexia profile was developed by the group of Bauer et al., based on weight loss, food intake and inflammatory status. These variables were investigated by determination of dietary intake, body composition, nutritional status, functional capacity and QoL in subjects with CC receiving chemotherapy [6].

As reported, the QoL is significantly impaired in CC subjects and there is evidence for increased morbidity and mortality of subjects with CC [5]. Subjects suffering from CC commonly have derangements in basal metabolic rate as well as reduced appetite and food intake. Even moderate weight loss is associated with psychological stress and lower QoL. Furthermore, CC affects subject's surgical risk and response to first- and second-line chemo-/radiotherapy [5]. Cachectic subjects are difficult to guide through chemotherapy experiencing more severe side effects resulting in progressive cachexia. The outcomes of subjects with CC receiving chemotherapy can be improved parenteral nutrition (PN) [6]. Supplementation with PN improves the QoL in subjects with advanced CC [7]. There are also data indicating that PN has a synergistic effect with chemotherapy and results in better clinical outcome [6,7]. Further research in form of randomized controlled trials is required to confirm these results. Besides, it is important to establish criteria for starting PN in cancer subjects [8]. The European Society of Parenteral and Enteral Nutrition (ESPEN) recommend PN only for malnourished subjects but does not reflect situation in CC patients. Furthermore, there is no recommendation of routine use of PN during chemotherapy, radiotherapy or a combined therapy [5,9].

At present, no 2^nd ^line therapy (or higher) is recommended for pancreatic adenocarcinoma, but often asked for [10]. In this clinical trial 5-FU (5-fluorouracil), folinic acid (FA) and oxaliplatin will be given as chemotherapy according to the OFF-scheme developed in the context of the clinical trial CONKO-003 [11]. This trial proofed a clinical benefit of 5-FU plus oxaliplatin as 2^nd ^line chemotherapy for subjects suffering from pancreatic adenocarcinoma. The reported median Overall Survival (OS) of 5 months is significantly higher than in the control group receiving 5-FU and FA (4.1 month; *p *= 0.014). Data from literature report median OS ranging from 4.3 month to 6.5 month [12,13]. Nevertheless, more scientific work is required to show that 2^nd ^line chemotherapy especially in combination with PN can improve the QoL in subjects suffering from pancreatic cancer.

## Methods/Design

### Trial organization

PANUSCO is designed and coordinated by the Department of Surgery, University of Heidelberg and the National Center for Tumor Diseases (NCT) in Heidelberg. Heidelberg is responsible for overall trial management, regulatory affairs, statistical planning and analysis, trial registration (International Standard Randomised Controlled Trial Number (ISRCTN60516908), http://www.controlled-trials.com) and reporting as well as quality assurance. The responsibility for external monitoring and pharmacovigilance is carried forward to independent Contract Research Organisations (CRO). The trial will be performed at four University Hospitals in Germany. The trial is sponsored by the foundation "Leben mit Krebs" in Germany. The financial sponsor is not involved in the data base management and has no access to the randomisation code.

### Investigators

Patients will be recruited by the four planned study sites. Special contracts will be disposed with the involved study centres. Due to the multimodal nature of the trial, all investigators will either be experienced oncologists or gastroenterologists. Additional, for the NI experienced nutritionists will take care for PN and BSNC.

### Data Safety Monitoring Board

An independent Data Safety Monitoring Board (DSMB) consisting of three experts (one expert in pancreatic carcinoma, one expert in nutritional medicine and one expert in biostatistics) will evaluate the clinical research data on an ongoing basis to assure patient safety and study integrity for the clinical trail. The board will monitor the trial data, in particular the safety data, and makes recommendations based on the periodically reviewed data. Responsibilities are laid down in a DSMB Charta.

### Medication supply

All chemotherapeutic agents will be prepared and provided by the corresponding pharmacy. Chemotherapeutic medication will be prepared for each patient specifically and delivered just prior to administration to the outpatient's department. PN will be applied overnight at patient's home by medical-experienced staff. Therefore, PN will be prepared at pharmacies next to the patient's home.

### On-site monitoring

Monitoring will be done by personal visits from clinical monitors according to the Standard Operating Procedures (SOPs) of the independent, external CRO. Monitors will review the entries into CRFs on the basis of source documents (30% source data verification). Data management will be performed by the Institute of Medical Biometry and Informatics (IMBI) at the University of Heidelberg. Pharmacovigilance is outsourced to a further CRO specialized on safety issues. Both data bases will be aligned at the end of the trial.

### Ethics, informed consent and safety

The final protocol was approved by the ethics committee of the University of Heidelberg, Medical School at September 22^nd^, 2009. The clinical trial complies with the Helsinki Declaration from 2008, the Medical Association's professional code of conduct, the principles of Good Clinical Practice (GCP) guidelines and the Federal Data Protection Act. The trial will also be performed in keeping with local legal and regulatory requirements. The medical secrecy and the Federal Data Protection Art will be followed.

Written informed consent for the clinical trial PANUSCO and respectively separate informed consent for the accompanying translational research will be obtained from each participating patient in oral and written from before inclusion in the trial. The nature, scope and possible consequences of the trial have been explained by a physician in detail. The investigator will not undertake any measures for the clinical trial or the translational research until valid consent has been obtained.

### Patient selection

PANUSCO focuses on hospitalised patients over 18 years of age suffering from advanced pancreatic adenocarcinoma with previous progression under chemotherapy.

Men and women over 18 years with histological confirmed advanced pancreatic adenocarcinoma which have received at least one previous chemotherapy (gemcitabine-based) will be screened for participation in the clinical trial. Patients will be contacted first-time by the (sub-) investigators at the outpatient's department. A detailed overview of recruitment criteria for inclusion and exclusion is given in table 1.

**Table 1 T1:** Eligibility Criteria

Inclusion criteria	Exclusion criteria
Written informed consent (IC)	Major surgery < 4 weeks prior to enrolment
Histological confirmed advanced pancreatic adenocarcinoma	Weight loss > 2% within the last seven days or caloric intake ≤ 500 kcal expected within the next five days
At least one previous chemotherapy (gemcitabine-based)	PINI-Index > 10
≥ 18 years old	Pregnancy or breastfeeding
Body weight ≥ 50 and ≤ 95 kg	> 4 weeks of parenteral nutrition within the last 6 months
BMI ≥ 19	Parenteral nutrition < 4 weeks prior to enrolment
Negative pregnancy test (females of childbearing potential)	Vulnerable populations (e. g. subjects incapable of giving consent personally)
Willingness to perform double-barrier contraception during study	Subject selection conflicts with warnings, precautions and contraindications stated for any investigational product
Expected life expectancy > 3 months	

### Study design

PANUSCO is an open label, controlled, prospective, randomized, multicentre phase IIIb trial with two parallel study arms (Figure 1). All Patients receive chemotherapy (a combination of 5-flourouracil (5-FU), folinic acid (FA) and oxaliplatin) at an outpatient's basis at the study sites. Additional, the patients in experimental group receive BSNC expanded with PN containing a total of 1150 kcal for each application. PN will be given by medical-experienced staff overnight at patients home. The control group receives solely BSNC consisting of nutritional advice. Every kind of enteral nutrition and oral supplementation is allowed for patients in both study arms.

**Figure 1 F1:**
[figure not shown]

### Study objectives

Primary objective is the comparison of the treatment groups with respect to event-free survival (EFS). EFS is defined as the time from randomization till time to development of an event defined as either an impairment (change from baseline of at least ten points in EORTC QLQ-C30, functional domain total score) or withdrawal due to fulfilling the special defined stopping criteria for chemotherapy as well as PN and Best Supportive Nutritional Care (BSNC) in Arm A or BSNC alone in Arm B or death from any cause (whichever occurs first). Chemotherapy will be continued until individual stop-criteria (disease progression, unacceptable toxicity) are met. This is unaffected by the (dis-) continuation of NI in both study arms. NI in both arms will be stopped when two of the three following criteria are met:

1. weight loss > 2% within the last seven days or caloric intake ≤ 500 kcal expected within the next five days,

2. BIA (Bioimpedance Analysis) defined by phase angle and body cell mass (BCM) with a deterioration > 10% (in both parameters)

3. Prognostic Inflammatory and Nutritional Index (PINI) > 10 (only in subjects with no sign of acute inflammation).

This is unaffected by the (dis-) continuation of chemotherapy.

Secondary objectives are the comparison of the treatment groups with respect to tumour-cachexia, Objective Response Rate (ORR), Time to Progression (TTP), Progression Free Survival (PFS), Overall Survival (OS), Toxicity, time from randomization till time point when stopping criteria are met. Furthermore, the definition and evaluation of a scoring system identifying subject groups who will benefit from second line chemotherapy and/or PN.

Accompanying translational research is focussing mainly on molecular signalling as well as on inflammatory parameters. The available results will be correlated with the clinical parameters.

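### The nutritional part of EFS is dated by the act of withdrawal, not by the criteria being met, so late or omitted stops in this open-label trial could shift EFS differently by arm

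*Protocol article*

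**What the plan says.** The abstract (Methods/Design) lists, among the events that end EFS, "withdrawal due to fulfilling the special defined stopping criteria for chemotherapy as well as for nutritional intervention (NI) or death from any cause". Study objectives repeats this by arm: "withdrawal due to fulfilling the special defined stopping criteria for chemotherapy as well as PN and Best Supportive Nutritional Care (BSNC) in Arm A", or from BSNC alone in Arm B. In both places the event is the withdrawal, with the criteria as its cause.

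The same section lists a secondary objective worded on the criteria themselves: "time from randomization till time point when stopping criteria are met".

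The rule behind the withdrawal is common to the arms: "NI in both arms will be stopped when two of the three following criteria are met". The three criteria rest on weight or intake, bioimpedance (BIA) and the PINI index. Two parts need a forecast or a judgement: "caloric intake ≤ 500 kcal expected within the next five days", and the restriction of the PINI criterion, "only in subjects with no sign of acute inflammation".

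Study design states that the trial is open label. Arm A receives PN at home overnight on top of BSNC. For Arm B, "The control group receives solely BSNC consisting of nutritional advice".

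**The concern.** Meeting a criterion is a state of the patient. Withdrawal is something staff do, knowing the arm. The primary endpoint counts the second. The act also carries different weight by arm: in Arm A it ends a nightly infusion, in Arm B it ends advice. A stop might be put off in Arm A because it matters, or go unrecorded in Arm B because little changes.

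Under the wording as it stands, two patients with the same weight, BIA and PINI values on the same day can have different EFS times. In the intention-to-treat (ITT) analysis, a patient who meets two of three criteria but continues NI has no nutritional event at that point. If such slippage differs between arms, the primary log rank test picks up a difference in conduct as well as any effect of PN.

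**Working it through.** **1. The plan's own figures reproduce** (inputs from Interim analysis and Sample size estimation).

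- HR = ln(0.6)/ln(0.4) = 0.5575.
- Schoenfeld, fixed design: 4 × (1.96 + 0.8416)² / (ln 0.5575)² = 91.96, so 92 events. With a two-stage O'Brien-Fleming design at half the information, 93 is the smallest number with power of at least 0.80 (0.801). The nominal one-sided levels come out at 0.0026 and 0.0240.
- Exponential EFS, 36 months' accrual plus 4 months' follow-up: event probability 0.952 (control) and 0.871 (experimental), mean 0.911. Then 93/0.911 = 102, and 102/0.85 = 120.

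No stated number is wrong. The point concerns the definition of the event.

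**2. The wordings side by side.** The primary endpoint names withdrawal because of the criteria, the secondary names the criteria being met, and the stopping rule says NI stops when they are met. With full adherence, act and criterion fall together. They separate only when a stop is late or does not happen, and then only the primary endpoint is affected.

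**3. What slippage could do with no true effect.** The document gives no component frequencies, so the shares, delays and omission rates are assumptions. NI withdrawal alone is taken to be an event.

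- Total hazard λ = −ln(0.4)/4 = 0.229 per month in both arms (the planned control rate), split into s·λ for NI-criterion events and (1 − s)·λ for all others, independent of each other.
- Arm B: event at the earlier of the two times. Arm A: the NI time is delayed by 4 weeks, or removed in 25% of patients, or both.
- HR from a Cox model on 200,000 or more patients per arm. Two-sided error with 93 events: δ = |ln HR| × √93 / 2, error = Φ(δ − 1.96) + Φ(−δ − 1.96). Example, HR 0.87: δ = 0.139 × 9.64/2 = 0.67, error = 0.099 + 0.004 = 0.10.

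| NI share s | 4-week delay | 25% omitted | both | error, both |
|---|---|---|---|---|
| 10% | 0.98 | 0.97 | 0.96 | 5% |
| 20% | 0.96 | 0.94 | 0.91–0.92 | 7% |
| 30% | 0.94–0.95 | 0.90–0.91 | 0.86–0.87 | 10–12% |
| 40% | 0.92 | 0.87 | 0.81–0.82 | 16–17% |

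Ranges cover runs with and without administrative censoring. A 2-week delay alone gives 0.96 to 0.99.

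A simpler check thins the hazard, HR = 1 − s·m, where m is the fraction not acted on. With s = 20% and m = 50%, HR = 0.90, and under the O'Brien-Fleming bounds the one-sided chance of a false win for PN is 0.073 instead of 0.025.

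**4. Two things that pull this back.**

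- *Other events soon follow.* At s = 30% with delay and omission together, if the hazard of the other events is 2, 3 or 4 times higher once the criteria are met (assumed), HR is 0.91, 0.93 or 0.94 and the error about 7.5% falling to 6%. Omission alone then gives 0.95 to 0.98.
- *Arm B slips too.* Equal slippage in both arms gives no false difference. Slippage in Arm B only mirrors the table: 1/0.98 = 1.02 to 1/0.82 = 1.22, against PN.

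**The case against.** The strongest reply is that the stop is not discretionary. Study objectives makes it mandatory, identical in both arms and based mainly on measured values. A patient kept on NI after meeting two criteria is a protocol deviation, not something the plan permits. This stands, and it removes the reading a reader might be tempted by: that EFS turns on a free clinical decision, or that it is biased towards PN. The document supports neither. The discretion lies only in imperfect adherence, which can occur in either arm.

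It can also be said that the two wordings may be meant as one date, with the secondary objective simply isolating the component. That is possible: the article does not show that two dates were intended, and the full analysis plan may settle the derivation. But the operative definition of the primary endpoint, given twice, names the act.

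The safeguards in the article help only in part. The interval-censored alternative (Primary analysis) addresses lag in recording events. A late withdrawal recorded on its own date shows no such lag, and an omitted one is no event. The per protocol analysis (Secondary analyses) does not redefine the event. Source data verification covers 30% (On-site monitoring).

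Finally, the simulation is generous to the concern. It perturbs Arm A only, treats an omitted stop as never recurring, and assumes independence from death and quality-of-life impairment, although the Background calls cachexia a strong predictor of both mortality and reduced quality of life. These criticisms stand, and step 4 shows their effect.

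**Conclusion.** The point holds as a weakness in how the primary endpoint is worded, not as a demonstrated bias. If the two-of-three rule is followed, act and criterion nearly coincide and little is lost. If stops are late or omitted to a different degree by arm, EFS shifts, and the direction is open.

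The size cannot be derived from the document. With assumed NI shares of 10% to 40%, and a 4-week delay, 25% omission or both in Arm A only, a null HR appears as about 0.98 to 0.82. It lies closer to 1 if meeting the criteria soon leads to another EFS event or if Arm B stops also slip. Heavier omission would go further, but that would need a mandatory rule to be broken on a large scale in one arm.

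One further assumption: the phrase joining the chemotherapy and NI criteria is read as meaning that an NI stop alone is an event. If both stops were required, the NI date would matter less often.

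**What to change.** In the abstract and Study objectives, date the nutritional component of EFS at the first assessment at which two of the three criteria are met. Derive it by the same rule from the recorded weight or intake, BIA and PINI values in both arms, whether or not NI was stopped. Use the same date for the secondary endpoint, and report by arm how often the criteria were met without NI being stopped.

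The cost is about one sentence in the definition and a derivation from values the rule already requires. The rule for stopping NI is not touched. The 93 events, 102 patients and 120 enrolled stand, provided the assumed EFS rates refer to this definition.

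There are two downsides. A few patients will count as events while still receiving NI. And the judgements on expected intake and on acute inflammation remain unblinded, so the change removes discretion over whether and when to act, not over whether the criteria are judged to be met.

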#### Experimental group

Additionally, patients in experimental group receive a total amount of 1036 ml PN, applied over night via port system. The PN will be administered continuously six days a week. An interruption will be performed during chemotherapy. Beyond, an adjournment of the PN up to two days is possible; an adjournment of three days is only once possible during participation of the clinical trial.

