### Evaluation, toxicity-based dose adjustment and follow-up

All patients must have appropriate lab and radiographic studies conducted prior to study enrolment to meet eligibility criteria. Lab parameters will be obtained at least weekly and imaging will be performed every seven weeks. The patient will be asked at each visit for any adverse event (AE) as well as concomitant medication and pain medication. Quality of life (QoL) questionnaires (QLQ-C30 and the pancreas specific PAN 26 questionnaire) will be handed out to all patients on day 1 and day 22 of each cycle prior to chemotherapy. Decisions regarding weekly chemotherapy treatment and chemotherapy dose-adjustment will be made using the guidelines below and based on haematological parameters monitored once weekly during chemotherapy. In case of grade 3 or grade 4 haematological toxicities chemotherapy should be held until resolution or until toxicity has resolved or dropped to grade 2. PN will be continued. The procedures for patients with leukocytes between 1.0/l and 1.5/l will be discussed individually in the study group. In case of grade 3 or grade 4 gastrointestinal toxicities (including anorexia, dehydration, nausea/vomiting, diarrhoea, mucositis and bleeding) patients will be considered for periodic outpatient intravenous rehydration with anti-emetics according to conventional practice guidelines. Any grade ≥ 2 neurotoxicity should lead to discontinuation of chemotherapy until recovery to at least grade 1. All uncertain cases of toxicities will be discussed by the study group discretion.

Patients can withdraw from study participation at any time. Patients are taken off the study if unacceptable toxicity appears. Unacceptable toxicity is defined as serious side effect or irreversible grade 4 toxicity, independent whether they are expected or unexpected. After the individual ending of the study subjects will receive the best available medical and nutritional care. Patients will undergo imaging and lab analysis (including tumor marker) quarterly and will be tracked by quarterly phone follow-up until death.

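### The protocol contradicts itself on whether unacceptable toxicity ends chemotherapy alone or the whole study, and leaves the EFS status of these patients open

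*Protocol article*

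**What the plan says.** All references are to the Protocol article.

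- **Study objectives, chemotherapy.** "Chemotherapy will be continued until individual stop-criteria (disease progression, unacceptable toxicity) are met". The next sentence adds: "This is unaffected by the (dis-) continuation of NI in both study arms". Treatment scheme repeats that the cycles run until progression or unacceptable toxicity.
- **Study objectives, nutritional intervention.** "NI in both arms will be stopped when two of the three following criteria are met". The three criteria are weight loss or low expected intake, bioimpedance deterioration, and a PINI above 10 in patients without acute inflammation. The section then states that NI in turn does not depend on whether chemotherapy goes on.
- **Evaluation, toxicity-based dose adjustment and follow-up.** "Patients are taken off the study if unacceptable toxicity appears". Such toxicity is defined as a serious side effect, or a grade 4 toxicity that cannot be reversed, whether or not it was expected. No causing treatment is named. After study end the section lists quarterly imaging, laboratory tests and telephone contact until death.
- **Experimental group.** Apart from the interruption during chemotherapy, the section limits pauses in PN: "an adjournment of the PN up to two days is possible; an adjournment of three days is only once possible during participation of the clinical" … Nothing says whether these limits cover interruptions for toxicity.
- **Study objectives, EFS.** Events are a QLQ-C30 loss of at least ten points, death, or withdrawal for meeting the stopping criteria for chemotherapy *as well as* those for NI.

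**The concern.** Unacceptable toxicity is given two different consequences. One set of sentences treats it as the end of one component of treatment, with the other component continuing. Another sentence treats it as the end of study participation. A site cannot follow both for the same patient.

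Two things depend on the choice. The first is whether the patient stays on protocol NI, which is parenteral nutrition (PN) plus best supportive nutritional care (BSNC) in the experimental arm and BSNC alone in the control arm. The second is how the patient enters the primary analysis. The trial is open label, so the route could be chosen with knowledge of the arm. Stopping for toxicity is also plausibly related to a patient's quality of life and prognosis, so censoring at that point may not be independent of the outcome.

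**Working it through.** **The plan's own figures.** No stated number is in dispute, and the planning figures reproduce:

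- HR = ln(0.60)/ln(0.40) = 0.557.
- Schoenfeld events, fixed design: 4 × (1.960 + 0.842)² / (ln 0.5575)² = 92.0.
- The two-stage O'Brien-Fleming inflation of 1.0078 gives 92.7, so 93 events.
- The mean event probability with 36 months of accrual and 4 of follow-up is 0.911, and 92.7/0.911 gives 102 patients.
- 102/0.85 = 120 enrolled.

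None of these depends on how a toxicity stop is handled, so they cannot size the problem.

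**Step 1: the two rules side by side.**

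| Case | Study objectives and Treatment scheme | Evaluation and follow-up section |
|---|---|---|
| Unacceptable toxicity of chemotherapy, either arm | Chemotherapy stops; NI goes on | Patient leaves the study, and so leaves protocol NI |
| Serious side effect of PN, experimental arm | Chemotherapy does not depend on whether NI goes on | Patient leaves the study, and so leaves study chemotherapy |

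The first row is a plain contradiction. The second is weaker. The definition names no causing treatment, so a serious PN side effect may itself meet the chemotherapy criterion. Chemotherapy would then stop on its own rule, not because NI stopped.

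**Step 2: the EFS status.** The words joining the two sets of stopping criteria allow two readings.

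- *Either set is enough.* Removal for unacceptable toxicity meets a chemotherapy criterion and is an event on that date.
- *Both sets must be met.* Removal for toxicity alone is no event. Secondary analyses censors patients with incomplete follow-up at their last follow-up date.

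If the site instead follows Study objectives, only chemotherapy stops. The patient has not clearly withdrawn from the study, and could remain at risk for a later EFS event. One clinical course therefore has three possible codings: event, censored, or still under follow-up.

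**Step 3: what is lost after removal.** The QLQ-C30 is scheduled on days 1 and 22 of each chemotherapy cycle. The follow-up listed after study end contains no QLQ-C30. Deaths would still be found, but a ten-point loss would not. Under the second reading, the quality-of-life component is therefore unobserved after removal.

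**Step 4: the pause limits.** Experimental group limits how long PN may be adjourned without giving a reason for the limit. It can be read as an adherence allowance or as a limit that also binds during toxicity. It does not resolve the conflict in Step 1.

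**The case against.** The strongest reply is that this is a journal article. Detailed handling of toxicity, post-study assessments and event coding may all sit in the full protocol. That stands for anything merely absent, and no missing PN toxicity rule is claimed here. It does not answer two printed rules that disagree.

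A second reply is that leaving the study does not mean all treatment ceases, since the article promises the best available medical and nutritional care afterwards. That is fair as to care. Such care is not protocol NI, however, and the EFS status stays open.

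A third is that EFS keeps death and quality-of-life loss as events in the intention-to-treat population, and that toxicity and adverse events are reported separately. This limits the harm, but only while quality of life is still measured.

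A reader might infer something stronger: that PN cannot be stopped for its own complications except by removing the patient, and that the resulting bias falls on the PN arm alone. The documents do not support this:

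- The NI criteria say when NI will be stopped. They do not say that nothing else may stop it.
- Uncertain toxicities go to the study group, and patients may withdraw at any time.
- "This is unaffected by the (dis-) continuation of NI in both study arms" itself envisages NI ending while chemotherapy goes on.
- Treatment scheme has a catheter implanted before treatment in both arms, so catheter complications are not confined to PN.
- A count such as 3 to 9 patients (5% to 15% of the 120/2 = 60 in the PN arm) rests on a complication rate that no document gives.

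**Conclusion.** The contradiction is real. Study objectives and Treatment scheme make unacceptable toxicity a chemotherapy stop with NI continuing, while the evaluation and follow-up section makes it a study exit. It is clearest for chemotherapy toxicity, which can occur in either arm, and less clear for a serious PN side effect. The EFS consequence is undetermined, and censoring at removal could be informative because the listed follow-up has no QLQ-C30.

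Neither the size nor the direction of any bias can be computed. The documents give no rate of unacceptable toxicity for either treatment or arm, and do not say which reading of the EFS definition applies. The conclusion rests on the printed text alone; a full protocol might already settle the point. On what is printed, the wording should be corrected, because it leaves a component of the primary endpoint to site interpretation in an open-label trial.

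**What to change.** The investigators should:

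1. Reconcile Study objectives, Treatment scheme, Experimental group, and the evaluation and follow-up section on what unacceptable toxicity ends: chemotherapy, NI or study participation. They should also say whether the limits on PN pauses apply to interruptions for toxicity.
2. State one rule for whether a stop for unacceptable toxicity is an EFS event, settle whether one set of stopping criteria is enough or both are needed, and apply it identically in both arms.
3. For any stop not counted as an event, continue QLQ-C30 and EFS follow-up, so that the intention-to-treat analysis is not informatively censored at that point.

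The cost is protocol wording, a case report form code for the reason for stopping, and a few further questionnaires for patients who have stopped treatment. No clinical stopping rule or threshold is proposed; those decisions remain with the investigators.
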